##### Evaluation

Evaluation is planned and carried out based on S.M.A.R.T. (specific, measurable, attainable, realistic and timely) criteria. Here, health data of the patients (from the eHealth platform, as well as from the nephrology GP system and the hospitals EMR) in the project, as well as of historical control patients, must be extracted, exported and analyzed in cooperation with MHH biometry resources.

S.M.A.R.T. criteria:

**A** Evaluation of care provider needs on data and information sharing, acceptance and feasibility (qualitatively, interviews with GPs / pediatricians) at 30 months.

**B** Implementation of a cross-sector eHealth platform including teleconsultations and patient access. Indicator: 50% of patients with shared use of the platform after 30 months.

**C** Implementation of a decision support system for GFR deterioration and cardiovascular comorbidities. Indicator: System is implemented at 30 months.

**D** Comparison of intersectoral treatment quality between Hannover Region and Erlangen. Indicator: Analysis performed at 30 months.

**E** Reduction of complications of nephrological diseases. Indicator: Reduction of complications requiring inpatient treatment. Indicator: A 10% reduction of hospital expenditure within 30 months compared to a control cohort (historical control patients who did not participate in the program).

**F** Reduction in cardiovascular events. Indicator: The number of hospitalizations due to cardiovascular events will be reduced > 10% within 30 months.**G** After the establishment of NEPHRO-DIGITAL, participant quality of life will improve significantly. Indicator: In the mental subscale of the SF-12, 80% of the participating patients will reach values which do not differ from population norm data within 30 months.

**H** Is the use of the new digital elements and the quality of life gender-dependent? Does a migration background play a role in the acceptance of digital medicine? Indicator: Participation rate in subgroups is not significantly different after 30 months.

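### Criterion H scores a non-significant subgroup difference as success, which is not evidence of similar participation, and its only indicator does not cover its own question on quality of life by gender

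*Protocol article*

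**What the plan says.** The Evaluation section of the protocol article lists eight S.M.A.R.T. criteria, A to H. Criterion H puts two questions: "Is the use of the new digital elements and the quality of life gender-dependent", and "Does a migration background play a role in the acceptance of digital medicine". The first has two parts, use and quality of life. One indicator follows for all of this: "Participation rate in subgroups is not significantly different after 30 months". No margin, confidence interval, significance level or subgroup size goes with it.

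The only quality-of-life indicator in the list is in criterion G, with its time limit counted in months: "In the mental subscale of the SF-12, 80% of the participating patients will reach values which do not differ from population norm data within 30". It applies to participating patients as a whole and is not broken down by gender. The nearest thing to an expected level of use is the target in criterion B: "Indicator: 50% of patients with shared use of the platform after 30 months".

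**The concern.** There are two separate problems.

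First, the indicator is met when a test fails to reject equal rates. A test can fail to reject because the rates are close or because there are too few patients to tell, and the rule does not distinguish the two. A project with a small migration-background subgroup would meet it almost by default. A very large project could miss it over a gap that nobody would care about. The result then reflects the sample size as much as the behaviour of the subgroups.

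Second, the indicator does not match the question. A participation rate says nothing about whether quality of life differs between men and women, and no other indicator in the list does so.

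H is the only criterion that asks whether one gender or patients with a migration background take up the platform less. As written, it could be reported as met while one group participates at a clearly lower rate.

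**Working it through.** **No stated figure to reproduce.** The article gives no sample size, power, significance level or margin for H. The inputs below are assumptions, chosen to show how the rule behaves:

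- Two-sided significance level 5%.
- True participation 40% v 50% (10-point gap) or 35% v 50% (15-point gap). The 50% is borrowed from the target in criterion B, which is not an observed rate.
- Subgroup sizes from 30 v 270 to 5000 v 5000.

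**Probability that the indicator is met.** For a pooled two-sample test of proportions, let d be the true gap and p̄ the pooled rate, with

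- s0 = √[p̄(1 − p̄)(1/n1 + 1/n2)]
- s1 = √[p1(1 − p1)/n1 + p2(1 − p2)/n2]

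Then P(met) = Φ((1.96·s0 − d)/s1) − Φ((−1.96·s0 − d)/s1).

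Worked case, 50 v 250 with 40% v 50%:

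- p̄ = (50 × 0.40 + 250 × 0.50)/300 = 0.483
- s0 = √(0.2497 × 0.024) = 0.0774
- s1 = √(0.24/50 + 0.25/250) = 0.0762
- (1.96 × 0.0774 − 0.10)/0.0762 ≈ 0.68, so Φ ≈ 0.752. The other tail is about 0.0005, giving P(met) = 0.751.

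| Subgroup sizes | True rates | Gap | Indicator met |
|---|---|---|---|
| 30 v 270 | 40% v 50% | 10 points | 82.5% |
| 50 v 250 | 40% v 50% | 10 points | 75.1% |
| 150 v 150 | 40% v 50% | 10 points | 58.7% |
| 200 v 800 | 40% v 50% | 10 points | 28.1% |
| 50 v 250 | 35% v 50% | 15 points | 50.9% |
| 5000 v 5000 | 48.5% v 51.5% | 3 points | 14.9% |

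In the last row s0 and s1 are both 0.010, so (0.0196 − 0.03)/0.010 = −1.04 and Φ = 0.149. The indicator fails in about 85% of repetitions for a 3-point gap. Among the rows with a 10-point gap, the chance of success falls from 82.5% to 28.1% although the gap stays the same.

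**What a margin would demand.** Near 50% participation the standard error of the difference is √[0.25(1/n1 + 1/n2)], and the half-width of the 90% interval is 1.645 times that. The last column takes the true rates as identical.

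| Subgroup sizes | 90% half-width | Chance that the interval lies within ±10 points |
|---|---|---|
| 30 v 270 | about 16 points | none |
| 50 v 250 | about 13 points | none |
| 150 v 150 | 9.5 points | about 7% |

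For 80% power at a true difference of zero, with smaller-subgroup share s and margin m, N = 0.25(1/s + 1/(1 − s))(1.645 + 1.282)²/m². For ±10 points the total is 857 (50/50 split), 1339 (20/80) and 2379 (10/90). For ±15 points it is 381, 595 and 1058.

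**Question against indicator.** This part needs no arithmetic.

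| Asked in H | Indicator in the list |
|---|---|
| Use of the digital elements by gender | Participation rate in subgroups (H) |
| Acceptance by migration background | Participation rate in subgroups (H) |
| Quality of life by gender | None; the SF-12 indicator in G covers all participants together |

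**The case against.** The strongest reply concerns weight. H is the last of eight project indicators, some of which only record that a system is in place or an analysis done. The primary hypothesis is about patient care, costs and quality of life and mentions neither gender nor migration background. The Discussion makes roll-out depend on positive effects and transferability without naming H. All of that stands, and it limits the importance of the point.

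It is also fair that the figures rest on assumed sizes and rates. The article describes a platform for all regional nephrology patients, so numbers could be large, and splits such as 30 v 270 fit migration background better than gender. That limits the figures but not the argument: the dependence on sample size follows from the form of the rule, and large samples bring the opposite error.

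A reader might infer three stronger things that the document does not support:

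- *That the project claims to have proved equal access.* The article makes non-significance the mark of success; it does not speak of proof or equality.
- *That quality of life by gender will never be analysed.* A statistical analysis plan that is not shown could include it. What can be said is that the indicator fixed here does not cover it.
- *That the participation rate cannot be calculated because data on eligible non-participants will not be extracted.* Participation can be read as platform use among project patients, as in criterion B, and those patients' data are to be extracted. The article's description of data extraction does not settle whether a recruitment record is kept.

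**Conclusion.** The point holds and should be fixed. It is not critical, because it does not alter the primary hypothesis. As written, the indicator for H treats lack of evidence of a difference as success, and this is a rule stated in the article rather than a detail left to another document. On the assumed inputs, a 10-point gap passes in roughly three of four repetitions with 50 v 250 patients and in 28% with 200 v 800, while a 3-point gap fails about 85% of the time with 5000 v 5000. Other sizes, rates or significance levels would change these percentages but not the dependence on sample size. The mismatch between H's question on quality of life by gender and its indicator rests on the text alone and needs no assumption.

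**What to change.** Replace the indicator for H with estimates. Report the difference in participation by gender and by migration background, each with a 95% confidence interval. Claim no relevant difference only if the 90% interval (two one-sided 5% tests) lies wholly within a margin that the project sets in advance; otherwise report a difference or state that the result is inconclusive. For the quality-of-life part, add a comparison of the SF-12 mental score by gender, with its confidence interval, as a second indicator.

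The change is one of wording plus one further analysis of SF-12 data already needed for criterion G. The real cost is that success becomes harder to claim. With a few hundred patients or a small subgroup, a tight margin such as ±10 points will usually or always give an inconclusive result, so the margin should be chosen with the expected subgroup sizes in view. If those sizes cannot support any useful margin, the differences and intervals should be reported without a success claim.

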## Discussion

The Nephro Digital project contributes to digitalization of nephrology with the aim of achieving a substantial improvement in the care of nephrologic patients. The focus of the project is the development of a new interoperable platform for health professionals and nephrologic patients. In an interdisciplinary consortium of clinical centers, computer scientists and software experts as well as an innovative e-health SME, a CDSS for nephrologic patiens will be developed. This utilizes data (e.g., lab values, weight, and blood pressure) from different sources to detect early worsening of health and to prognose future deterioration of kidney function and cardiovascular events. The CDSS ​​system will inform the physician about these risks. The physician can then structurally integrate these parameters, which have so far not been systematically collected, into his decision-making and thus has a better data basis for the diagnosis and therapy decision. Thus, medical experience and CDSS complement each other in the sense of an “augmented intelligence” from which both doctor and patient benefit.

If the positive effects of our project could be confirmed and if the transferability in other regions is confirmed by the implementation of the CDSS in Erlangen, it is planend to implement the structures into routine care in the region Hannover and in other areas that are interested.

## Data Availability

Not applicable.

## Abbreviations

CDSS: Clinical Decision Support System
eFA: Electronic case file
GP: General Practitioner
IHE: Integratig the Healtcare Enterprise
KRH: Regional Hospital Hannover
KTX: Kidney transplantation
MHH: Hannover Medical School
SDO: Starrd developing organisations
UKER: University Hospital of Erlangen
